## 5.7 Sample Size

The primary clinical outcome is uncorrected visual acuity in the study eye on the ETDRS logMAR chart at a starting distance of 4 metres at 3 months following surgery, ascertained by an optometrist masked to the trial group. A change in visual acuity of 1 line of the chart is considered to be clinically important, one logMAR line is 5 letters (each letter is 0.02 logMAR) and the test-retest variability is reported as 0.07 logMAR. If there is truly no difference in mean logMAR between the two groups, then 432 patients (216 per group) would provide 90% power to be sure that a 95% two sided confidence interval would exclude the non-inferiority limit of 0.1 logMAR, assuming a common standard deviation (SD) of 0.32. The SD is from the Royal College of Ophthalmologists’ National Ophthalmic Database of unaided vision 3 months following cataract surgery (n= 20,155).

However, although treatment is delivered on an individual basis, each patient cannot be assumed to generate independent information since they will be clustered within surgeons. To take account of clustering by surgeon (i.e. the variation between surgeons in the treatment effect) the sample size must be increased by an inflation factor f = 1 + (m-1)*p. Assuming a total of 16 surgeons contribute and an average cluster size (m) of 50 (patients/surgeon) and an estimated ICC (p) of 0.012, this yields an f of 1.59. A total of 688 patients (344 per group) would enable the trial to take account of clustering by surgeon. To allow for an anticipated 15% dropout rate (the mean age of patients undergoing cataract surgery is 75 years old and many have significant systemic comorbidities) the total sample size required is 808 patients (404 per group). The sample size calculation was conducted using Stata/IC version 12.1 (StataCorp, College Station, TX, USA. The IDMC will be asked to review all the assumptions used for the sample size calculation before the end of recruitment.

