## 5.9 Assignment of Intervention

### 5.9.1 Allocation

#### 5.9.1.1 Sequence generation

Patients will be randomised in a 1:1 ratio to either surgical procedure via the Sealed Envelope.com website. Sealed Envelope is a randomisation service provider that provides a proven, reliable and centralised randomisation system. The system will be custom designed to the trial requirements.

This will use minimisation with a random element with stratification by a) treatment centre, b) surgeon, and c) whether in the local clinician’s opinion, the patient will require surgery on one or both eyes.

A random trial arm allocation will be computer generated. Sealed Envelope will provide the randomised treatment for each participant.

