### 5.10.4 Statistical Methods

#### 5.10.4.1 Statistical Analysis Plan

The primary analysis will be conducted following the intention to treat principle where all randomised patients are analysed in their allocated group whether or not they receive their randomised treatment. Baseline characteristics will be summarised for each treatment groups. Continuous data will be summarised using means and standard deviations, if data appear Gaussian, or medians and interquartile ranges. Binary data will be reported as proportions and percentages.

All statistical tests will use a 2-sided P value of 0.05 unless otherwise specified. All confidence intervals presented will be 95% and two sided. A detailed statistical analysis plan will be developed for approval by the Trial Steering Committee and review by the Independent Data Monitoring Committee and finalised before the first substantive statistical analysis. All statistical analyses will be performed using Stata (StataCorp, College Station TX, USA).

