#### 5.10.4.2 Statistical Methods – Outcomes

The primary outcome is uncorrected distance visual acuity at 3 months following surgery on the study eye, measured using an ETDRS chart at a starting distance of 4 metres. Mean UDVA will be reported together with a two-sided 95% confidence interval. This will be compared between treatment groups using regression analysis adjusting for baseline habitual logMar^[[1]](#footnote-2)^ visual acuity and the randomisation stratifiers (treatment centre, surgeon, and whether or not patients have one or both eyes eligible). We will include trial site in our regression models as a fixed effect and surgeon as a random effect. If the upper end of the 95% CI for the difference between means does not cross the non-inferiority limit of 0.1 logMAR, then laser surgery will be regarded as non-inferior. If the mean difference is negative and its 95% CI lies wholly to the left of zero, then we can conclude that laser surgery is superior to manual surgery. We will perform sequential testing of the non-inferiority and superiority hypotheses.

Secondary continuous outcomes such as uncorrected distance visual acuity at 12 months, corrected distance visual acuity and patient reported outcome measures Catquest-9SF will be analysed in a similar fashion. The percentage of study eyes experiencing adverse events (e.g. posterior capsule tears, dropped lens) in the two groups will be compared using Fisher’s exact tests.

In addition regression analyses will be performed for continuous outcomes such as corrected distance visual acuity at 12 months for the study eye, adjusting for baseline habitual logMar visual acuity and the randomisation stratifiers (treatment centre, surgeon, and whether or not patients have one or both eyes eligible). Baseline habitual logMar visual acuity is only collected for the study eye and therefore distance visual acuity outcomes for the fellow eye, whether they are unaided or corrected, will only be adjusted for the randomisation stratifiers.

Pearson’s correlation coefficients (or Spearman’s rank correlation coefficients, depending on the distribution of the data) will be used to assess the relationships between the continuous objective and subjective outcome measures.

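### The sample size allows for surgeon-to-surgeon variation in the treatment effect, but neither the nested-design formula nor the surgeon term named in the primary model matches that variation with surgeons crossed with arms

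*Protocol*

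**What the plan says.** **Sample size (Protocol 5.7).** The calculation starts from "432 patients (216 per group) would provide 90% power", on the premise "If there is truly no difference in mean logMAR between the two groups" and the criterion that a "95% two sided confidence interval would exclude the non-inferiority limit of 0.1 logMAR", with an SD of 0.32. It continues: "To take account of clustering by surgeon (i.e. the variation between surgeons in the treatment effect) the sample size must be increased". With 16 surgeons, it takes "an average cluster size (m) of 50 (patients/surgeon) and an estimated ICC (p) of 0.012, this yields an f of 1.59". This gives 688 evaluable patients, and 808 after 15% dropout.

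**Design.** Patients are randomised individually, 1:1, by "minimisation with a random element with stratification by a) treatment centre, b) surgeon" and by one or both eyes (5.9.1.1). Section 5.3.1.4 sets one experience requirement that a surgeon must meet before operating in either arm.

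**Analysis (5.10.4.2).** The primary regression adjusts for baseline acuity and the stratifiers: "We will include trial site in our regression models as a fixed effect and surgeon as a random effect". Non-inferiority is read from the upper limit of that model's interval, and section 5.10.4.1 adds: "All confidence intervals presented will be 95% and two sided". No surgeon-by-treatment term is named. The interactions planned in 5.10.4.3 concern one or both eyes and trial site, not surgeon.

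**The concern.** Three parts of the protocol imply three different variance structures for the same comparison.

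- The stated reason for inflation is that the laser effect differs from surgeon to surgeon.
- The formula, with m equal to a surgeon's whole caseload over both arms (16 × 50 = 800), is the usual one for clusters that lie wholly within one arm.
- The model names surgeon as a random effect, ordinarily an intercept. An intercept absorbs differences in outcome level that a surgeon carries into both arms, and these cancel from the comparison anyway.

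If the first is true and the model has only an intercept, the standard error behind the non-inferiority decision is too small, and the mistake favours declaring non-inferiority. If there is no such variation, the interval is sound but the 90% power is not the power of this trial. The variation is not far-fetched: the entry requirement is 10 completed laser operations (5.3.1.4), and surgeons choose their own method of correcting astigmatism (5.4.1.1, 5.4.2.1).

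**Working it through.** **Inputs.** From 5.7: margin 0.1 logMAR, true difference 0, SD 0.32, one-sided 2.5% (two-sided 95% interval), 16 surgeons (k), m = 50, ICC p = 0.012, 688 analysed (N). Assumed, because the protocol gives no value: tau, the SD between surgeons of the treatment effect. Equal caseloads and 1:1 allocation within surgeon are also assumed.

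**1. The plan's own figures.**
- Per group: 2 × (1.96 + 1.2816)² × 0.32² / 0.1² = 215.2, so 216, total 432.
- f = 1 + 49 × 0.012 = 1.588.
- 216 × 1.59 = 343.4, so 344 per group, total 688. Added patients: 688 − 432 = 256.
- 432 × 1.588 / 0.85 = 807.1, so 404 per group, total 808.

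The arithmetic reproduces.

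**2. Variance with surgeons crossed with arms.** A surgeon effect shared by both arms drops out, leaving

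Var(difference) = 4 × SD² × (1 − p) / N + tau² / k.

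The first term is 4 × 0.1024 × 0.988 / 688 = 0.000588, with square root 0.0243. This is the standard error that an intercept-only model targets. The design effect is the total variance divided by 4 × 0.1024 / 688 = 0.000595.

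**3. A range for tau.** Suppose 0.012 is the share of outcome variance that lies between surgeons within an arm. The between-surgeon variance in each arm is then 0.012 × 0.1024 = 0.00123, and tau² = 2 × (1 − c) × 0.00123, where c is the correlation between a surgeon's mean results in the two arms. This gives tau = 0 at c = 1, 0.035 at c = 0.5, 0.050 at c = 0 and 0.070 at c = −1. To reproduce f = 1.588, tau must satisfy 1.588 × 0.000595 = 0.000588 + tau²/16, so tau is about 0.076.

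**4. Results at N = 688.** Power = Φ(0.1/SE − 1.96). The 15 df column uses the noncentral t distribution. The error of an intercept-only interval at the margin is 1 − Φ(1.96/r), with r = SE/0.0243.

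| tau (logMAR) | Design effect | SE | Power, normal | Power, 15 df | One-sided error, intercept only |
|---|---|---|---|---|---|
| 0 | 0.99 | 0.0243 | 98.5% | 97.0% | 2.5% |
| 0.035 | 1.12 | 0.0258 | 97.2% | 95.2% | 3.3% |
| 0.050 | 1.25 | 0.0272 | 95.7% | 92.9% | 4.1% |
| 0.070 | 1.50 | 0.0299 | 91.7% | 87.7% | 5.6% |
| 0.076 | 1.59 | 0.0307 | 90.2% | 86.0% | 6.1% |

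Power drops below 90% once tau exceeds about 0.076 (normal) or 0.062 (15 df).

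**5. Simulation check.** With 20,000 replicates and 42 patients for each of 16 surgeons, the intercept-only error was 2.7%, 3.1%, 4.0% and 6.0% at tau 0, 0.035, 0.050 and 0.076. With an illustrative uneven caseload (4 to 110 patients per surgeon, 688 in all) it was 2.5%, 3.8%, 4.7% and 8.3%.

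**The case against.** **The protocol never says intercept only.** Section 5.10.4.1 promises a detailed analysis plan, and the structure of a random effect and its degrees of freedom are commonly settled there. A random surgeon effect that includes a treatment slope would carry the variation named in 5.7. This stands, and it makes the error inflation conditional. A reader might infer that no reading reconciles the two sections on the interval; the text does not support that. What remains is that 5.7 fixes a rationale and 5.10.4.2 fixes the surgeon term and the decision rule without linking them.

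**The formula may be nearly right.** Suppose 0.012 is a surgeon-by-treatment component, meaning a deviation of opposite sign in the two arms with variance p × SD². Then tau² = 4 × p × SD², and the crossed design effect is exactly 1 + (m − 1)p: 1.50 at m = 688/16 = 43, and 1.59 at m = 50. This also stands, and it is why the meaning of the ICC has to be stated before any other factor is written in. A reader might substitute 1 + 24 × 0.012 = 1.288, using 25 patients per surgeon per arm. That value assumes a surgeon's results in the two arms are uncorrelated, and it counts randomised rather than analysed patients, so the documents do not establish it. The reading that rescues 5.7 is also the one on which an intercept-only interval does badly (5.6%).

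**The sample size errs on the safe side.** Section 5.7 also has the data monitoring committee review the assumptions before recruitment ends. Both are true. That review cannot judge an ICC whose meaning is not given.

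**Conclusion.** The inconsistency is real. The stated 90% is the power of a design with surgeons nested in arms, or of this design only if tau is near 0.076 logMAR. For tau from 0 to 0.050, power at 688 analysed is 98.5% to 95.7%, and still 92.9% on 15 df at 0.050. An intercept-only interval would have a one-sided error of 2.5% to 4.1% over the same range.

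A reader might go further in three ways that the documents do not support:

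- **That the trial is underpowered.** On the outcome-level reading of the ICC, with a surgeon's results in the two arms uncorrelated or positively correlated, it is not.
- **That the error rate is about 6%.** This needs tau near 0.076, above even the 0.070 that perfect negative correlation gives on that reading. It also needs real variation and an intercept-only model.
- **That 808 should be 810.** Dividing the already rounded 688 by 0.85 gives 809.4, but the unrounded chain gives 807.1. The gap is rounding.

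The conclusion rests on an assumed range for tau, 16 surgeons with equal caseloads, an SD of 0.32 and the ordinary reading of the surgeon term. With no effect variation, the planned interval is valid.

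**What to change.** 1. **Section 5.7.** State whether the ICC of 0.012 describes outcome level or surgeon-by-treatment variation. Use a variance formula for surgeons crossed with arms, and restate the inflation factor and power on that basis, with a range for tau if it is unknown. Keep 808.
2. **Section 5.10.4.2.** Add a random surgeon-by-treatment coefficient to the random surgeon intercept, and use small-sample degrees of freedom suited to about 16 surgeons (Satterthwaite or Kenward-Roger). Say how these combine with Rubin's rules, and make the imputation in 5.10.5, which is run separately by group, compatible with surgeon effects that differ by arm.
3. **Alternative to 2.** If effect variation between surgeons is judged negligible, withdraw that rationale from 5.7, state the power without it, and keep a random intercept, named as such.

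Settle the choice before any comparative data are seen, because it determines the decision interval. The cost is revised text in two sections, some work to align the imputation, and a somewhat wider interval under option 2. No extra recruitment follows.

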### 5.5.2 Secondary Outcomes

*Secondary outcomes (all time points relate to times after cataract surgery in the study eye)*

- Uncorrected distance visual acuity (UDVA) at 12 months following surgery on the study eye.
- Corrected distance visual acuity (logMAR) at 3 and 12 months following surgery on the study eye (ETDRS logMAR chart at a starting distance 4 metres).
- Ocular complications within 3 and 12 months of surgery on the study eye. A complication will be defined as any event that causes unintentional injury to an ocular structure, or requires additional treatment, or has a negative effect on a patient's health or eyesight.
- Uncorrected and corrected visual acuity (using the ETDRS chart at a starting distance of 4 metres) and complications in the second eye (for those with bilateral cataracts), and with both eyes open at 3 and 12 months following surgery on the study eye.
- Proportion of patients with vision within 0.5 and within 1 dioptre of intended refractive outcome (and second eye for those with bilateral cataracts) at 3 and 12 months following surgery on the study eye.
- Quality of life as measured by the EQ-5D-3L questionnaire+vision bolt-on question (EQ-5DV) at 6 weeks, 3, 6 and 12 months.
- Patient reported vision health status using Catquest-9SF (26) at 3, 6 and 12 months.
- Cost-utility analysis reported as the incremental cost-effectiveness ratio and cost-effectiveness acceptability curves.
- Corneal endothelial cell count (additional safety measure) in both eyes, at 3 and 12 months following surgery on the study eye.

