## 5.6 Participant Timeline

**Figure 1: Schedule of Assessments**

|  | Standard pre-assessment (for study and non-study patients) | **Baseline** | **Randomisation** | **Follow up** | | | | |
| --- | --- | --- | --- | --- | --- | --- | --- | --- |
|  |  | Surgical Pre Assessment Visit | Randomisation and surgery | Standard non-study post-op appt | 6 weeks post-surgery (by post)  (ideally +/-14 days) | 1^st^ trial apt: 3 months post-surgery  (ideally +/-14  days) | 6 months post-surgery  (by post)  (ideally+/-14  days) | 2^nd^ trial apt: 12 months post-surgery  (ideally +/-14 days) |
| Visit Number | *1* | *1 or later* | 2 | *3* |  | *4* |  | *5* |
| Past medical and ocular history | X | X |  |  |  |  |  |  |
| Consent for cataract surgery | X |  |  |  |  |  |  |  |
| Informed Consent & eligibility screening |  | X |  |  |  |  |  |  |
| Identification of study eye |  | X |  |  |  |  |  |  |
| Visual acuity: UDVA, pinhole, +/- glasses (Snellen), each eye | X |  |  | X |  |  |  |  |
| Visual Acuity: UDVA^1^ & CDVA^2^ (logMAR) each eye and binocular |  |  |  |  |  | X |  | X |
| Visual acuity (LogMAR) with usual method of correction |  |  | X^7^ |  |  |  |  |  |
| Subjective refraction |  |  |  |  |  | X |  | X |
| Ocular biometry | X |  |  |  |  |  |  |  |
| Pentacam corneal topography | X^6^ | X |  |  |  | X |  | X |
| Optical coherence tomography (OCT)^3^ | X^6^ | X^8^ |  | X^6^ |  | X |  | X |
| Inclusion/Exclusion Criteria |  | X |  |  |  |  |  |  |
| Catquest-9SF questionnaire |  | X |  |  | X | X | X | X |
| EQ-5D-3L+vision bolt-on question (EQ-5DV) |  | X |  |  | X | X | X | X |
| CSRI^5^ |  | X |  |  |  | X | X | X |
| Endothelial cell count measurement | X^6^ | X^8^ |  |  |  | X |  | X |
| Surgery |  |  | X |  |  |  |  |  |
| Adverse Event Collection |  |  |  |  | X | X | X^4^ | X |

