# 10 Appendices

## 10.1 Specular microscopy for obtaining central corneal endothelial cell density – Standard Operating Procedure

- Central corneal endothelial cell density (CCED) and morphology will be measured using a non-contact specular microscope.
- Coefficient of variation of cell size (COV), and the percentage of hexagonality (HEX) will also be recorded to indicate the degree of polymorphism and pleomorphism respectively.
- Calculation of endothelial cell loss:
- Percentage change in CCED at each time point from baseline

= (Preop CCED – CCED at each time point)/Preop CCED x 100

1. Visual acuity (logMAR) with the patient’s usual method of correction (current glasses or unaided). [↑](#footnote-ref-2)

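### Section 5.10.4.2, read literally, adjusts Catquest-9SF for visual acuity and leaves out the Catquest-9SF baseline that the trial collects

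*Protocol*

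**What the plan says.** Section 5.10.4.2 compares the primary outcome between arms by "regression analysis adjusting for baseline habitual logMar" acuity and the stratifiers: treatment centre, surgeon, and one or both eyes eligible. For secondary continuous outcomes it says that "patient reported outcome measures Catquest-9SF will be analysed in a similar fashion". The next paragraph returns to the same covariate: "In addition regression analyses will be performed for continuous outcomes such as corrected distance visual acuity at 12 months for the study eye", again with baseline habitual acuity and the stratifiers. Fellow-eye acuity is adjusted for the stratifiers only, on the stated ground that habitual acuity is collected for the study eye alone. No other baseline covariate is named in the section.

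Section 5.5.2 lists "Patient reported vision health status using Catquest-9SF (26) at 3, 6 and 12 months" as a secondary outcome. Figure 1 has a row for the "Catquest-9SF questionnaire" with a mark in the baseline column as well as at follow-up.

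For the corneal endothelium, section 5.5.2 lists the cell count in both eyes at 3 and 12 months. Figure 1 schedules "Endothelial cell count measurement" before surgery and at both visits. Appendix 10.1, the specular microscopy procedure, defines cell loss as "Percentage change in CCED at each time point from baseline", that is, preoperative minus follow-up density, divided by preoperative density, times 100. Section 5.10.4.2 names no model for this outcome.

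**The concern.** Catquest-9SF is the patient-reported outcome named in the structured summary. Its own baseline score would ordinarily be expected to predict follow-up better than acuity in one eye, and it is already being collected. A statistician who follows section 5.10.4.2 to the letter would adjust for acuity and leave that score out. Minimisation (section 5.9.1.1) uses centre, surgeon and one or both eyes, so nothing in the design balances baseline Catquest-9SF between arms; adjustment is the direct protection against a chance difference. By contrast, section 5.10.6.1 does provide for adjusting the utility analysis for baseline differences if necessary.

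The endothelial count raises a smaller question. It is called an additional safety measure, but three places leave its analysis open: the outcome list gives a count, the appendix derives a percentage, and the statistical section is silent.

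What is at stake is the precision of secondary comparisons and clarity about which covariates are fixed in advance.

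**Working it through.** **The plan's own figure.** The only sample size is for the primary outcome (section 5.7). With margin 0.1, SD 0.32, one-sided 0.025, 90% power and true difference 0:

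- n per group = 2 × 0.32² × (1.960 + 1.282)² / 0.1² = 215.2, so 216, or 432 in total, as stated.
- f = 1 + 49 × 0.012 = 1.588; 432 × 1.588 = 686.0 (686.9 with f = 1.59), against 688 stated.
- 688 / 0.85 = 809.4, against 808 stated.

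The figures reproduce to within two patients. They use no baseline correlation and concern uncorrected distance acuity only, so nothing below changes them. The protocol gives no figure for Catquest-9SF or cell count.

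**Catquest-9SF.** All three correlations are assumptions:

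- r, baseline with follow-up Catquest-9SF: 0.2 to 0.6
- v, baseline acuity with follow-up Catquest-9SF: 0 to 0.3
- c, between the two baselines: 0.3 (r, v and c taken in absolute value, with consistent signs)

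The right comparator is the model already adjusted for acuity, with residual variance proportional to 1 − v². With both baselines in the model,

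R² = (r² + v² − 2rvc) / (1 − c²), and the variance ratio is (1 − R²) / (1 − v²).

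At r = 0.5, v = 0.2: R² = (0.25 + 0.04 − 0.06) / 0.91 = 0.2527; ratio = 0.7473 / 0.96 = 0.778.

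| r | v = 0 | v = 0.1 | v = 0.2 | v = 0.3 |
|---|---|---|---|---|
| 0.2 | 0.956 | 0.968 | 0.978 | 0.985 |
| 0.3 | 0.901 | 0.919 | 0.934 | 0.947 |
| 0.4 | 0.824 | 0.848 | 0.868 | 0.884 |
| 0.5 | 0.725 | 0.755 | 0.778 | 0.797 |
| 0.6 | 0.604 | 0.639 | 0.666 | 0.686 |

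Inverting, omission leaves residual variance higher by 1/0.985 − 1 = 1.5% up to 1/0.604 − 1 = 66%; the middle case gives 1/0.778 − 1, about 28%. In confidence interval width, √0.778 = 0.88, so the interval would be about 12% narrower with the Catquest-9SF baseline included.

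Swapping acuity out for baseline Catquest-9SF is not always a gain: at r = 0.2, v = 0.3 the ratio is (1 − 0.04) / (1 − 0.09) = 1.055. That is a reason to let acuity stay alongside.

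**Endothelial count.** Simulation with assumed baseline mean 2500 (SD 300), follow-up mean 2250 (SD 300 or 400) and baseline to follow-up correlation 0.3 to 0.9. Efficiency is relative to regression of the follow-up count on the baseline count:

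| Correlation | Percentage change, follow-up SD 300 | Percentage change, follow-up SD 400 |
|---|---|---|
| 0.3 | 0.690 | 0.843 |
| 0.5 | 0.799 | 0.942 |
| 0.7 | 0.906 | 0.983 |
| 0.9 | 0.984 | 0.763 |

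Unadjusted percentage change therefore costs about 2% to 31% if it is the analysed variable. With baseline added as a covariate its efficiency is 0.97 to 0.98. Against the raw follow-up count (SD 300), percentage change has relative efficiency 0.76 at correlation 0.3, 1.07 at 0.5, 1.77 at 0.7 and 5.2 at 0.9, so it does draw on the baseline.

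**The case against.** The best defence is that analysing Catquest-9SF in a similar way could mean the same form of model with each outcome's corresponding baseline. For uncorrected acuity, habitual logMAR acuity is that baseline, since Figure 1 marks logMAR uncorrected and corrected acuity only at 3 and 12 months. The fellow-eye sentence fits this reading: the study-eye covariate was not carried over to an eye it does not describe. The paragraph that repeats the acuity covariate gives corrected acuity as its example and does not mention Catquest-9SF. A detailed statistical analysis plan is promised in section 5.10.4.1 and may name the covariates.

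Part of this stands. The protocol nowhere says that acuity replaces the Catquest-9SF baseline; that is the literal reading of the cross-reference, not an express statement. But the section names one baseline covariate, applies it to continuous outcomes generally, discusses the case where a baseline is missing, and does not mention the Catquest-9SF baseline that exists. An analysis plan faithful to the text could inherit the omission.

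A reader might also infer that the protocol turns cell count into percentage change and so wastes its baseline. The documents do not support that. The listed outcome is the count, the formula appears only in a measurement procedure, no text makes it the between-group variable, and percentage change uses the preoperative value as both reference and denominator.

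A reader might measure the Catquest-9SF gain as 1 − r², a reduction of 9% to 36% for r between 0.3 and 0.6. That compares with a model that has no baseline covariate, which is not what section 5.10.4.2 describes.

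**Conclusion.** The point holds for Catquest-9SF on the literal reading of section 5.10.4.2. An already collected baseline is left out of the main patient-reported comparison, at a cost in residual variance described by a ratio of about 0.60 to 0.99, and 0.78 in the middle case. The range rests wholly on assumed correlations; at its upper end the loss is negligible.

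For endothelial cell count the finding is only that sections 5.5.2 and 5.10.4.2 and Appendix 10.1 leave the analysed variable and its covariates open.

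A reader might infer bias, or a threat to the trial's main conclusion. Neither follows. The randomised comparison is unbiased with either covariate, and the primary analysis, the margin and the sample size are untouched. Participants are not masked (section 5.9.2), but baseline adjustment would not remove bias from unmasked self-report, so that fact adds nothing here. The change is worth making because it gains precision at no data cost and removes later discretion over covariates.

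**What to change.** In section 5.10.4.2, state that each continuous secondary outcome is adjusted for its own baseline value where one is collected, together with the randomisation stratifiers. For Catquest-9SF this means modelling the score at 3, 6 and 12 months on baseline Catquest-9SF plus the stratifiers; habitual acuity may stay as an additional covariate.

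In the same place, state that follow-up endothelial cell count is compared between arms with the same eye's baseline count as covariate, and that the percentage loss in Appendix 10.1 is reported descriptively.

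The cost is a change of wording in the protocol, carried into the statistical analysis plan before the first substantive analysis. It needs no new data, visits or patients.
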